## Methods

### Study Design

#### Clinical and Health Economic Evaluation

For the organization and evaluation of the new form of care, a stepped-wedge design was chosen [36,37]. In a stepped-wedge design, there are different clusters that start recruitment at the same time in the control phase. The individual clusters then move gradually into the intervention phase in randomized cohorts. In the EXPERT project, there is a transition phase between the control and intervention periods, which serves to implement and test the new form of care in the individual clinics as well as train the staff.

Randomization in the EXPERT project will take place at the hospital level. There are 31 hospitals participating in the study. Each clinic forms a cluster that belongs to 1 of 4 cohorts. The clusters within a cohort always enter the next study phase (transition or intervention phase) at the same time. The study will be conducted over a period of 24 months (18-month recruitment period+6-month follow-up of the last enrolled person). Data collection regarding the individual course of treatment takes place from the time of enrollment in the patient sample until 6 months later. Figure 2 shows the planned course of the study in the stepped-wedge design.

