#### Work-Related Evaluation

Physicians and nurses who are or will be involved with the project take part in the work-related evaluation. With medium to small effect sizes (η^2^>0.05 and <0.15), a type-1 error (α) of 5%, and a type-2 error (β) of 20% (80% power), a minimum number of 120 people per measurement point is required for the work- and project-related evaluation (60 people each in the control and treatment groups). A total of 4 employees per clinic at measurement time t0 and 4 employees at measurement time t1 are included in the sample. This results in 31 × 8 = 248 elevations. Care is taken to interview physicians and nurses in equal parts, all of whom are or will be involved in the project measures.

Regarding the interviews for the assessment of the objectives and project implementation, 2 persons from the nursing service and 2 persons from the medical profession are to be interviewed at time t1 in the clinics that are already implementing the new form of care. Approximately 72 people from at least 18 clinics will take part in the interviews.

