Before the clinics of cohort 1 start implementing the new form of care in project month 7 (Figure 2), both the clinic staff of cohort 1 (treatment group) and the clinic staff of cohort 3 (control group) will be examined with the EXPERT questionnaire in project months 4 and 5 (measurement time Pre). In project months 12 and 13, clinic staff from both cohorts will repeat the questionnaire (measurement time Post). The same procedure will be followed for cohort 2 and cohort 4, 3 and 9 months later, respectively. Project staff from UKM will recruit enough people in the individual clinics for the surveys. Interested employees in the clinics who are or will be involved in the project can find out more about the survey in advance by means of an information text. The UKM project staff receive a questionnaire link as a QR code from the Steinbeis project staff for the corresponding measurement time tailored to the corresponding group and cohort and send this QR code to a contact person in the clinics. The contact persons pass on the QR code to the participants, who scan it on their mobile phones and answer the questions. Participants are requested to do so as soon as possible after receiving the link. The completed questionnaires are automatically stored anonymously on the Steinbeis University server and later evaluated in summary form.

The UKM staff draw attention to the project-related interviews in the clinics that are already implementing the measures. Interested employees can find out more about the interviews by means of an information text and can contact the Steinbeis project staff to make an appointment for the telephone interview. They then receive an email from Steinbeis with the confirmation of the appointment, the interview questions, and the (renewed) promise that their email address and telephone number will be deleted after completion of the project. The transcripts of the telephone interviews are anonymized using a code. The content collected in the interviews will be evaluated in summary form, quantitatively, and qualitatively.

Regarding the topics of workload, work engagement, work-related resources, and readiness for technology, the main effects and interactions between measurement time (before vs after start of the Extremity Board) and group of measures (treatment vs control) are examined via variance analysis; the result is a 2 × 2 design with the factors time (before vs after) and group (treatment vs control group).

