Ergonomic aspects of the telemedicine technology are collected and descriptively evaluated at the second measurement point in approximately half of the clinics.

As staff turnover in hospitals is high, it can be assumed that the groups of employees will be composed differently at each time of measurement. Therefore, no repeated-measure design can be applied. The analyses will be performed as balanced grouping factors with the same number of participants in all conditions (before vs after and treatment vs control). The measurements are considered as a grouping factor of a multiple ANOVA.

The evaluation of the repertory grids yields 2D representations of the negative and positive constructs mentioned by the interviewees during the interviews with respect to the different implementation steps, namely, preparation, development of new standards, interdisciplinary collaboration, and therapy implementation.

The combination of a questionnaire that can be used quickly and easily on a mobile phone and a telephone interview with both predetermined, scaled questions and open-ended evaluations according to the repertory grid technique results in a comprehensive picture of changes in pretest-posttest working conditions and of the success factors accompanying the process both in quantitative and qualitative terms. On the one hand, the web-based questionnaire before and after the introduction of the new form of care quantitatively captures influences on workload, work engagement, work-related resources, and readiness for technology and backs them up through the “difference-in-difference” design. On the other hand, central success factors regarding project implementation will be collected both quantitatively and qualitatively and made visible by means of the repertory grid technology as “mental maps” of the employees in the 31 participating clinics.

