## Results

The EXPERT project started in June 2022 with the necessary preparations and agreements among all partners involved. Patient data collection started in April 2023. As of June 13, 2024, data from 425 patients have been included. The web-based survey of clinic employees began in July 2023, and the interviews started in February 2024. So far, 146 people have taken part in the questionnaire survey, and 15 people have taken part in the interviews.

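### The staff-survey analysis calls for equal numbers in all four time-by-group cells, which 31 clinics with 4 staff each cannot supply without leaving out at least 8 of the 248 planned responses

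*Protocol article*

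**What the plan says.** Under Data Analysis, Work-Related Evaluation, the article describes a 2 × 2 analysis of variance with time (before, after) and group (treatment, control) as factors. Staff turnover is expected to be high, so different people are likely to answer at each time: "Therefore, no repeated-measure design can be applied". The next sentence says the analyses will be run with "balanced grouping factors with the same number of participants in all conditions".

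Three other places fix the numbers that feed those cells:

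- Study Design, Clinical and Health Economic Evaluation: "There are 31 hospitals participating in the study", and "Each clinic forms a cluster that belongs to 1 of 4 cohorts".
- Study Design, Work-Related Evaluation: cohorts 1 and 2 form the treatment group, cohorts 3 and 4 the control group.
- Data Sampling, Work-Related Evaluation: "A total of 4 employees per clinic at measurement time t0 and 4 employees at measurement time t1", which the article totals as 31 × 8 = 248. The stated minimum is 120 people per measurement point, 60 in each group.

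Participation is voluntary (Ethical Considerations), through a QR code passed on by a contact person in each clinic. The same section adds that project staff will recruit enough people. The Results section reports: "So far, 146 people have taken part in the questionnaire survey". It gives no breakdown by cell.

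**The concern.** The equal-numbers sentence is about how the analyses are done, so it reads as a condition on the data analysed and not only as a recruitment aim. Taken that way it conflicts with the sampling plan, because an odd number of whole clinics with a fixed number of staff each cannot yield equal groups. Nor does the article say what happens when the cells differ.

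The target of this evaluation is the time-by-group interaction, which is the difference-in-difference. If an analyst met the condition by cutting every cell to the size of the smallest, that contrast would lose precision. The choice of which responses to omit would be made after the data are in, without a stated rule. Balance is not needed for a valid estimate of the interaction when all four cells hold different people.

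**Working it through.** **Inputs from the article:** 31 clinics; whole clinics assigned to groups; 4 staff per clinic per time point; 248 responses in total; minimum 60 per cell; alpha 5%; power 80%; eta-squared between 0.05 and 0.15; 146 responses by 13 June 2024.

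**Assumptions, not in the article:** the number of clinics per group; all response rates; three of the four survey waves complete at 146 responses; the size of the smallest cell.

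**1. The plan's own figures.** 31 × 8 = 248 is exact. For an F test with 1 numerator degree of freedom and noncentrality N × η²/(1 − η²), 80% power needs N = 120 at η² = 0.0625, which lies inside the stated range. The ends of the range give N = 152 (0.05) and N = 47 (0.15). The minimum of 120 is therefore reproducible.

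**2. Can the cells be equal?** With a and b clinics in the two groups, a + b = 31, the cells hold 4a and 4b at each time point. Equality needs a = b = 15.5, which is impossible. Trimming to the smaller group leaves out 2 × 4 × |a − b| responses:

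- 16 against 15: cells of 64 and 60; 8 of 248 left out (3.2%).
- 17 against 14: cells of 68 and 56; 24 left out.

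The minimum is therefore 8.

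**3. Cost at full response.** The variance of the interaction contrast is σ² × Σ(1/n) over the four cells. With the effect held at the size that η² = 0.05 implies for equal cells, the noncentrality is 16 × (0.05/0.95) / Σ(1/n).

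| Cells | N | Σ(1/n) | Power |
|---|---|---|---|
| 64/64/60/60 | 248 | 0.06458 | 94.9% |
| 60/60/60/60 | 240 | 0.06667 | 94.3% |

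The difference is 0.6 percentage points.

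**4. Cost under random non-response.** Each of the 248 places was assumed to be filled independently with probability 60% to 95%, without replacement. All four cells were equal in under 0.1% of simulations. Trimming to the smallest cell discarded on average 11% of responses (60% response) down to 5% (95% response).

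**5. Cost under uneven response.** If 146 responses came from three complete waves of four, 146/3 × 4 ≈ 195 would arrive, an average of 48.75 per cell. A smallest cell 20% lower holds 39, and trimming keeps 4 × 39 = 156. At η² = 0.05:

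| Data used | N | Σ(1/n) | Power |
|---|---|---|---|
| All, one cell low (39/52/52/52) | 195 | 0.08333 | 88.5% |
| All, two cells low (39/39/58.5/58.5) | 195 | 0.08547 | 87.8% |
| Trimmed (39 in each) | 156 | 0.10256 | 81.3% |

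Trimming raises the variance of the contrast by 23% (0.10256/0.08333) or 20% (0.10256/0.08547) and costs about 7 points of power. All power figures ignore clustering of staff within clinics.

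**The case against.** A reader might infer that the plan will throw away valid responses. The article does not say so: nothing in it mentions discarding, trimming or subsampling. The sentence can be read as a description of the design, with time as a between-subject factor and cells planned to be equal. Continued recruitment or quotas are another route to equality, since project staff undertake to recruit enough people. A rule for unequal cells could also sit in an analysis plan that is not shown.

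A reader might also infer that equal cells cannot be reached at all. That is too strong. Fifteen clinics × 4 = 60, so four cells of 60 are attainable and match the stated minimum. What cannot be done is to reach equality and use all 248 planned responses.

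The larger loss rests on assumed figures. The total of 146 has no stated target for that date and no split by wave or cell. Even in the uneven case, trimmed power is 81.3%, above the 80% target, and at η² = 0.0625 it is 89.3%. Equal cells also bring some benefit: orthogonal effects and some robustness to unequal variances.

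These points limit the size of the problem. They do not remove the conflict between the equal-numbers sentence and the 31 × 4 sampling, and the benefits of balance do not require data to be left out.

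**Conclusion.** The point holds as a minor one on a secondary evaluation. The equal-numbers condition cannot be met under the stated sampling without leaving out at least 8 of 248 responses, voluntary response makes equality by chance very unlikely, and the model does not need it. At full response the cost is 3.2% of responses and 0.6 points of power, assuming the closest possible split of 16 against 15 clinics. It reaches about 7 points (about 88% to 81% at η² = 0.05) only under the assumed 195 responses with a smallest cell 20% below average. The document supports neither a claim that responses will be discarded nor a claim that serious power loss is to be expected.

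**What to change.** Delete the equal-numbers condition. State instead that all responses are analysed in a 2 × 2 linear model with time, group and their interaction, allowing unequal cells; that the interaction is tested from that model; and that the four cell counts are reported.

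A clinic effect would be desirable but should be added only if clinic is recorded with each response. The article describes anonymous questionnaires with QR codes specific to time, group and cohort, and does not list clinic among the details respondents give.

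The core change is a sentence or two of analysis wording and needs no new data. Recording clinic, if it is not already captured, would be a separate change to data collection with data-protection implications.

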## Results

The EXPERT project started in June 2022 with the necessary preparations and agreements among all partners involved. Patient data collection started in April 2023. As of June 13, 2024, data from 425 patients have been included. The web-based survey of clinic employees began in July 2023, and the interviews started in February 2024. So far, 146 people have taken part in the questionnaire survey, and 15 people have taken part in the interviews.

## Discussion

### Principal Findings

The aim of the EXPERT project is to improve the treatment of fractures with open soft tissue damage or postoperative complications rapidly and sustainably. To perform optimized multifaceted treatment, we consider the following disciplines an essential part of the interdisciplinary team: trauma surgeons, vascular surgeons, plastic surgeons, specialists for infectious diseases, radiologists, pharmacologists, hygienists, and microbiologists. We think that an interdisciplinary board needs several disciplines to not only enable a complete interdisciplinary treatment approach but also develop interdisciplinary treatment algorithms for infections or provide interdisciplinary prophylaxis in musculoskeletal surgery.

In addition to the evaluation of the clinical outcome, the cost reduction and cost-effectiveness of the new intervention will be evaluated based on claims data provided by 3 major statutory health insurance companies. The focus will be on use of health services and their cost as well as the duration of incapacity for work and HRQoL.

Furthermore, a process evaluation will explore the impact on workload, job satisfaction, and technology acceptance throughout the implementation phase and individual onboarding processes of the caretakers.

### Comparison to Prior Work

The establishment of standardized treatment pathways in the standard care of patients with open fractures and postoperative infections may increase the chances of recovery for those affected and reduce costs. The previous heterogeneity of treatment methods, which is not expedient, can be reduced. Through largely standardized diagnostics and therapy, processes in the clinics can be optimized, and service processes can be standardized. Unnecessary and redundant diagnostics and treatment steps may be avoided. At the same time, the interdisciplinary treatment perspective allows for a more individualized therapy. This study aims to show that this results in a reduction in direct treatment costs and length of stay in hospital as well as a reduction in secondary costs (eg, due to long sick leave after discharge and revisiting practitioners). This is also in line with previous research findings.

Fractures impact function, quality of life, and psychological well-being. An multidisciplinary approach and early diagnosis are crucial for treatment success. Interdisciplinary support and patient-tailored treatment shortens hospital stays and reduces treatment costs, and standardized treatment pathways optimize clinic processes and reduce unnecessary steps [69-71]. In particular, hospital stays and costs induced by fracture-related infections are reduced [72]. The importance of multidisciplinary collaboration is especially effective for patients with hip fractures [73].

### Strengths and Limitations

When measuring the quality of treatment in trauma surgery, several influencing factors must be considered. The type of injury, the extent of anatomical reconstruction during surgery, soft tissue management, perioperative management, and rehabilitation protocols as well as patient compliance have a major influence on the outcome and make evaluation difficult. For our study, we chose 4 outcome measures: the complication rate after initial surgery (nonunion, infection, unplanned surgical revision, and need for prolonged antibiotic therapy), the number of applied antibiotics, the functionality of the injured limb, and HRQoL.

The clinical outcome is examined using a stepped-wedge design, which allows for the statistical consideration of time effects. The design also has practical advantages, such as the easy implementation of a staggered rollout. Among the weaknesses of a stepped-wedge design are time-sensitive recruitment efforts, complex randomization requirements when assigning hospitals to different cohorts or wedges, the assumption of high treatment schedule fidelity, and effects of the observation (the so-called Hawthorne effect) [74].

We choose a difference-in-difference design, a widely used quasi-experimental design in clinical research, to evaluate work-related outcomes. This design eliminates confounding by comparing outcomes before and after treatment. However, the design relies on a parallel-slopes assumption, which is hard to manage and may not always apply [75].

### Conclusions

The interdisciplinary, cross-disciplinary, and cross-departmental coordination of service providers enables comprehensive interface management in the clinics. The perspective of service providers can increasingly focus on holistic, patient-oriented coordination of management processes, which provides patients with the best possible access to individualized therapy in a timely manner. In addition to health economic advantages, the multidisciplinary treatment is expected to improve the quality of the therapy, which is to be proven through clinical follow-up. In addition, it is conceivable to establish specialized outpatient or inpatient treatment centers for patients with open fractures and postoperative infections in which the new diagnostic and therapeutic pathways are competently applied.

## Appendix

Multimedia Appendix 1 Peer review report by the Deutsches Zentrum für Luft- und Raumfahrt e. V. (DLR) - DLR Projektträger - Bereich Gesundheit (Bonn, Germany).

## Abbreviations

EXPERT: Extremity Boards for process optimization, evaluation, risk minimization, and therapy optimization for fractures with soft tissue damage or postoperative infection of the lower extremities in the trauma network
HRQoL: health-related quality of life
*ICD-10*: *International Statistical Classification of Diseases and Related Health Problems, 10th Revision*
JD-R: job demands–resources
UKM: University Hospital Münster
